### 5.3 Inclusion Criteria

Both female and male patients are included in this clinical trial. Patients must meet all of the following inclusion criteria to be eligible for enrollment into the study:

1. PCR confirmed SARS-CoV-2 infection in a respiratory tract sample.
2. Oxygen saturation (SaO2) of 94% or less while breathing ambient air or a ratio of the partial pressure of oxygen (PaO2) to the fraction of inspired oxygen (FiO2) of less than 300 mm Hg.
3. High risk due to either

pre-existing or concurrent hematological malignancy and/or active cancer therapy (incl. chemotherapy, radiotherapy, surgery) within the last 24 months or less (group 1)

and/or

chronic immunosuppression not meeting the criteria of group 1 (group 2)

and/or

Age ≥ 50 -75 years meeting neither the criteria of group 1 nor group 2 (group 3)  
and at least one of these criteria:

Lymphopenia < 0.8 x G/l

and/or

D-dimer > 1µg/mL

and/or

Age ≥ 75 years meeting neither the criteria of group 1 nor group 2 (group 4).

4. Blood hemoglobin concentration ≥ 10g/dl.
5. Provision of written informed consent.
6. Patient is able to understand and comply with the protocol for the duration of the study, including treatment and scheduled visits and examinations.

7. Male or female patient aged  $\geq 18$  years
8. Postmenopausal or evidence of non-childbearing status. For women of childbearing potential: negative urine or serum pregnancy test within 14 days prior to study treatment.

Postmenopausal or evidence of non-childbearing status is defined as:

- Amenorrheic for 1 year or more following cessation of exogenous hormonal treatments
- Luteinizing hormone (LH) and Follicle stimulating hormone (FSH) levels in the post menopausal range for women under 50 except in patients with a history of surgical sterilisation (bilateral oophorectomy or hysterectomy)
- Radiation-induced oophorectomy with last menses > 1 year ago
- Chemotherapy-induced menopause with > 1 year interval since last menses
- Surgical sterilisation (bilateral oophorectomy or hysterectomy)
- Female patients of child bearing potential and male patients with partners of child bearing potential, who are sexually active, must agree to the use of highly effective forms of contraception. This should be started from the signing of the informed consent and continue throughout the study and for 1 month (female patients) / 3 months (male patients) after last infusion of CP

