**Table 2: Clinical Laboratory Measurements**

| Category                                    | Lab Parameters                                                                                                                                                                                                                                                                                                                                                                                                                  |
|---------------------------------------------|---------------------------------------------------------------------------------------------------------------------------------------------------------------------------------------------------------------------------------------------------------------------------------------------------------------------------------------------------------------------------------------------------------------------------------|
| Hematology (local lab)                      | Haemoglobin, RBC, platelets, WBC with differential cell counts at baseline. If absolute differentials are not available, % differentials should be provided.                                                                                                                                                                                                                                                                    |
| Blood chemistry and Coagulation (local lab) | BUN, creatinine, albumin, AST/SGOT, ALT/SGPT, total bilirubin, gGT, AP, LDH, lactate, sodium, potassium, magnesium, calcium, serum uric acid, LDH, Troponin, CK and CK-MB, Quick, PTT, ATIII, D-Dimer, INR, Fibrinogen, Ferritin, transferrin levels and transferrin saturation, CRP, total protein, albumin, IL6, procalcitonin, total IgG, IgA, IgM                                                                           |
| Viral Screen (local lab)                    | HAV, HBV, HCV, and HIV-1                                                                                                                                                                                                                                                                                                                                                                                                        |

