## 10.3 Sample Size Calculation

Based on recently published data median time to an improvement defined as two points on a seven point ordinal scale or live discharge from the hospital is assumed to be at day 16 from randomization. This median estimate considers patients who died without an improvement as censored at day 84 (right-censoring), which ensures that those patients are considered as “not improved” over the whole observation period. In our trial, we follow the same analysis strategy as in Cao *et al.*, 2020 who also censored deceased patients at the end of follow-up.

We assume that based on the mechanism of action (neutralizing antibodies) a rapid improvement is induced by fresh frozen plasma from subjects after convalescence of SARS-CoV-2 infection on two days from two different donors with a median time of 10 days (HR=1.6). Assuming exponentially distributed event times, these assumptions correspond to a hazard of  $\lambda_C = 0.043$  for the control arm, while the corresponding hazard in the experimental arm should amount to  $\lambda_E = 0.043 \cdot 1.6 = 0.69$ .

While it is allowed for patients from the control arm to switch to the experimental arm starting at day 10 (see section 6.8), we assume this will not have a major effect on the median time of clinical improvement for these patients, since we expect that plasma infusions will have a larger advantage if given early. While methods for handling patients switching from control to treatment group are available, they are subject to strong and unverifiable assumptions. Hence, we will ignore treatment switch in the primary analysis, representing a treatment policy strategy (see Section 10.2.1), which can be regarded as a conservative approach since switching is only allowed from the control to the experimental arm. However, in supplementary analyses of the primary endpoint, we will consider such a hypothetical scenario in which a treatment effect is estimated for the case that patients would not have switched by means of inverse probability censoring weighting according to Robins & Finkelstein, relying on the assumption that there are no unmeasured confounders influencing the probability to switch, and a rank preserving structural failure time (RPSFT) model, assuming a common treatment effect which remains constant over time, regardless when treatment is initiated.

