Since patients might die before experiencing a clinical improvement or being discharged from the hospital, death will be taken into account via censoring deceased patients at last day of follow-up (day 84). Based on recently published data, the mortality rate is assumed to be about 20% in the control arm. Thus, we expect that the cumulative improvement rate of the control group will not become larger than 0.8. Hence, fewer improvement events are expected during the follow-up of 84 days than under the assumption of an exponential distribution, since the improvement curves will flatten at some point. In case of the control group, the flattening is expected to occur at day 38, since the assumed cumulative improvement rate at day 38 amounts to  $\exp(-\lambda_C \cdot 38) = \exp(-0.043 \cdot 38) \approx 0.8$ . Accordingly, we conservatively assume a follow-up length of 38 days for the sample size calculation to properly estimate the probability of experiencing the event of interest, even though the actual follow-up for each patient will be longer.

To detect the assumed difference between treatment groups using a log-rank test comparing the cumulative improvement curves for the primary endpoint using a significance level of 5% (two-sided) with a power of 80%, a total number of 174 patients is required for the entire trial (87 patients per group) when additionally considering a dropout rate of 5%, meaning that n=164 patients who do not prematurely drop out of the study are required to be enrolled. The required number of events which was calculated using the formula by Schoenfeld, amounts to 142. It is expected that adjusting for the covariate “patient group” in the analysis will lead to an increase in power. Sample size calculation was done conservatively assuming an equally long follow-up period of 38 days for every patient. Sample size calculation was done using RPACT v 2.0.6.

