### **10.5.4 Analysis of the Primary Endpoint**

The primary analysis will assess the null hypothesis “the cumulative improvement curves for the primary endpoint in the experimental and control arm are equal”, i.e.  $H_0: S_E = S_C$  against the alternative hypothesis  $H_1: S_E \neq S_C$  at a two-sided significance level of  $\alpha=5\%$ . This will be achieved by using the log-rank test stratified for the factor “patient group” as used in the randomisation procedure. The event “death from any cause” will be handled by censoring those patients at day 84 (in analogy to the approach of Cao et al, NEJM 2020). Using this approach ensures that deceased patients are considered as “not improved” over the whole observation period of 84 days. The hazard ratio for treatment group will be determined using a Cox regression model stratifying for the factor “patient group” together with a 95% confidence interval. The cumulative improvement curves are calculated using the Kaplan-Meier method together with 95% log-log-type confidence bands, and will be calculated separately for both treatment groups. In addition, cumulative improvement curves will also be calculated separately for each patient group per treatment group.

The fact that some patients from the control group might switch to the experimental group at day 10 will be ignored in the primary analysis, representing a treatment policy approach

according to the ICH E9 (R1) addendum on estimands . Patients who drop out during the trial or are lost to follow-up are taken into account as censored observations. The primary analysis will be based on the FAS according to the ITT principle.

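### The primary analysis leaves baseline D-dimer and lymphocyte count unused, which is a missed efficiency gain and not an error in the design

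*Protocol*

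**What the plan says.** **Role of the markers.** In section 5.3, "Lymphopenia < 0.8 x G/l" and/or a D-dimer above 1 µg/mL is what admits a patient aged 50 to 75, outside groups 1 and 2, to group 3. Neither marker appears in the definitions of groups 1, 2 and 4. The synopsis expects 25% of patients in each group, so those three groups make up 75%.

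**Collection.** Table 2 (section 7.1) lists "Haemoglobin, RBC, platelets, WBC with differential cell counts at baseline" under haematology and "Quick, PTT, ATIII, D-Dimer, INR, Fibrinogen, Ferritin" within chemistry and coagulation. Section 7.1 has haematology, coagulation and chemistry measured at each visit until discharge, for all patients. It places randomisation after the baseline assessments are complete.

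**Analysis.** Section 10.5.4 specifies a log-rank test stratified by patient group, and then: "The hazard ratio for treatment group will be determined using a Cox regression model stratifying for the factor" patient group. No other covariate is named. The IPCW switching model in the same section uses patient group, ordinal scale and viral load. Elsewhere, laboratory values appear only in the baseline summaries (10.5.2) and the safety summaries.

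**On adjustment.** Section 10.3 expects that adjusting for patient group "in the analysis will lead to an increase in power".

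**The concern.** In a log-rank or Cox analysis, omitting a covariate that predicts the event moves the marginal hazard ratio towards 1 and costs power, even in a randomised trial. It also leaves chance imbalance in that covariate in the estimate.

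The protocol relies on adjustment for efficiency but confines it to patient group. The sample size calculation assumes the same median time to improvement in all four groups. Under that assumption the stratification factor carries no prognostic information, so no gain can come from it. Two continuous measurements that the protocol itself takes as signs of risk enter only as a dichotomy within one quarter of the sample.

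Power has no slack. The target is "using a significance level of 5% (two-sided) with a power of 80" per cent, and the first row of Table 3 already stands at 0.785.

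**Working it through.** **Inputs from section 10.3.** Control median 16 days, experimental median 10 days, HR 16/10 = 1.6, two-sided alpha 0.05, power 80%, 38 days of follow-up for the event probability, 5% dropout. From its simulation: group sizes 42/40/42/40 and 38-day mortality of 20% and 13%.

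**Step 1: reproduce the plan.**
- Events (Schoenfeld): 4 × (1.960 + 0.8416)² / (ln 1.6)² = 142.1. The protocol states 142.
- Event probability at 38 days: control 1 − exp(−38 × ln 2/16) = 0.807; experimental 1 − exp(−38 × ln 2/10) = 0.928; mean 0.868.
- Evaluable patients: 142.1 / 0.868 = 163.8, so 164. With dropout: 164 / 0.95 = 172.6, so 173, or 174 for equal arms.
- Table 3, first row: simulated with the stratified log-rank test, four strata, and patients who die unimproved held event-free to day 84 (4,000 runs). The result is 0.7845 against the stated 0.785.

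The stated figures reproduce with no marker in the model.

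**Step 2: assumptions the documents do not supply.**
- One SD of each marker changes the improvement hazard by a factor of 1.0, 1.1, 1.2, 1.3 or 1.5.
- The two markers correlate at 0.3.
- Every group 3 patient has at least one marker on the adverse side of an assumed cut at the median.

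**Step 3: planned test against adjusted test.** The planned test is the log-rank test stratified by group. The adjusted test is the Wald test from a Cox model stratified by group, with both markers as continuous covariates. Both were applied to the same simulated data. The Monte Carlo standard error of each power is about 0.01, for example √(0.78 × 0.22 / 2000) = 0.009.

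Calibration A holds the treatment HR at 1.6 given the markers. If times are exponential given the markers, each arm's median is inversely proportional to its baseline hazard. Arm medians of 16 and 10 days then imply a conditional HR of 16/10 = 1.6. There were two runs of 2,000 trials per row.

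| HR per SD, each marker | Planned | Adjusted |
|---|---|---|
| 1.0 | 0.782, 0.773 | 0.780, 0.782 |
| 1.1 | 0.779, 0.781 | 0.784, 0.787 |
| 1.2 | 0.768, 0.754 | 0.787, 0.784 |
| 1.3 | 0.728, 0.737 | 0.784, 0.792 |
| 1.5 | 0.672, 0.672 | 0.784, 0.778 |

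Calibration B raises the conditional HR so that the planned test roughly keeps its stated power (2,500 runs).

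| HR per SD | Conditional HR | Planned | Adjusted | Gain |
|---|---|---|---|---|
| 1.2 | 1.64 | 0.788 | 0.811 | 0.023 |
| 1.3 | 1.66 | 0.784 | 0.834 | 0.050 |
| 1.5 | 1.75 | 0.768 | 0.864 | 0.096 |

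The gain is similar under both calibrations. What differs is whether it makes good a shortfall (A) or adds to a plan already close to target (B).

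**Step 4: type I error.** With no treatment effect and 1.3 per SD (6,000 runs, standard error √(0.05 × 0.95 / 6000) = 0.003), rejection was 0.056 for the planned log-rank test and 0.060 for the adjusted Wald test. A small part of the apparent gain may therefore be liberality of the Wald test.

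**The case against.** The strongest reply is that nothing in the plan is wrong. A log-rank test stratified by the randomisation factor is valid and conventional, every planning figure reproduces, and the choice of further covariates is partly preference. The schedule also records SOFA, the frailty scale, CRP, IL-6, LDH and ferritin. This stands, and it is why the point concerns efficiency only. What singles out these two markers is that the protocol itself uses them to define risk.

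A reader might infer that the trial does lose power, down to 0.67, or that 174 patients are too few. The documents do not support that. They give no prognostic strength, and 0.67 needs a factor of 1.5 per SD for both markers together with calibration A. The 1.6 in section 10.3 is derived from the arm medians, with exponential times and no marker in the model. On calibration B the planned test stays at 0.77 to 0.79.

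A reader might also take a smaller unadjusted hazard ratio as bias. In a simpler simulation without deaths and with independent markers, it averaged 1.51 against a conditional 1.6 at a factor of 1.42 per SD. That is non-collapsibility: the marginal and conditional hazard ratios are different quantities, and the plan does not miss its own target.

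Three further objections stand and shape the fix:
- The protocol does not apply these markers to groups 1, 2 or 4. In haematological malignancy a lymphocyte count may mean something else, so one common slope is doubtful.
- Section 10.5.6 rules out imputation beyond what it describes, and Table 2 accepts percentage differentials.
- The baseline wording in Table 2 is attached to haematology. That D-dimer is available at baseline for every patient is inferred from section 7.1 and from its use as an entry criterion.

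**Conclusion.** The point holds as a missed efficiency gain. The protocol itself fixes a primary analysis on patient group alone, while two of its own risk markers are on the panel for all patients. Adjusting for them would gain nothing detectable at 1.0 to 1.1 per SD, about 2 to 3 points of power at 1.2, about 5 at 1.3 and about 10 at 1.5. There is no detectable loss of power if the markers are not prognostic.

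These figures rest on assumed prognostic strengths, a correlation of 0.3, a common slope across groups and a Wald test. The version with a separate group 1 slope and a score or likelihood-ratio test was not simulated. The sample size and the validity of the planned test are not in question.

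**What to change.** In section 10.5.4, keep the stratification by patient group and pre-specify log baseline D-dimer and log baseline absolute lymphocyte count (last value before randomisation) as continuous covariates in the Cox model that gives the reported hazard ratio and confidence interval. Show the unadjusted stratified estimate beside it.

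If the sponsor wants the gain in the test as well, take a score or likelihood-ratio test from that model, not a Wald test, and keep the stratified log-rank test as a sensitivity analysis.

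Supporting changes:
- Derive the absolute lymphocyte count from WBC and the percentage differential where only the latter is reported.
- Let the lymphocyte slope differ for group 1.
- Harmonise D-dimer units across the local laboratories.
- Add an exception to section 10.5.6 allowing simple replacement of a missing baseline covariate.
- State in section 10.2.1 that the hazard ratio is conditional on the markers.

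The cost is text in three sections and three extra parameters (two slopes and one group 1 difference) against about 142 events, with no new data. The choice should be fixed before outcomes are seen, because covariates chosen later in an open-label trial would carry little credibility.

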**CROSS-OVER OPTION into experimental arm:**

Cross-Over starts with baseline visit and follows the primary schedule of the study as described in the trial schedule (Table 1).

## **7.2 Methods of Data and Sample Collection**

### **7.2.1 Data Collection and Handling**

All findings including clinical and laboratory data are documented by the investigator or an authorized member of the study team in the patient's medical record and in the electronic case report forms (eCRFs). The investigator at the clinical site is responsible for ensuring that all sections of the eCRFs are completed correctly and that entries can be verified against source data. The eCRFs have to be filled out according to the specified CRF Completion Guidelines. The correctness of entries in the eCRFs is confirmed by dated signature of the responsible local principal investigator or deputy principal investigator.

## **7.2.2 Sample Collection and Handling**

For translational analysis samples are obtained at the times indicated in Table 1. Transport is done by TNT courier service or a similar operator providing the needed transport conditions. Further details are provided in the laboratory manual.

## **7.3 Measurement of Efficacy Parameters**

The endpoints are analysed according to established criteria as suggested by the WHO.

### **7.3.1 Seven point ordinal scale**

The seven point ordinal scale value is determined at the time of study inclusion and afterwards until discharge within 84 days after randomization or end of trial. This endpoint was also recommended by the WHO R&D Blueprint expert group (Coronavirus disease (COVID-2019) R&D. Geneva: World Health Organization (<https://www.who.int/blueprint/priority-diseases/key-action/novel-coronavirus/en/>)). The seven-category ordinal scale consists of the following categories: 1, not hospitalized with resumption of normal activities; 2, not hospitalized, but unable to resume normal activities; 3, hospitalized, not requiring supplemental oxygen; 4, hospitalized, requiring supplemental oxygen; 5, hospitalized, requiring nasal high-flow oxygen therapy, noninvasive mechanical ventilation, or both; 6, hospitalized, requiring ECMO, invasive mechanical ventilation, or both; and 7, death.

This scale is clearly defined and values will be obtained daily for each patient until day 28, thereafter weekly until day 56, then on day 70 and finally at day 84. A change in two points is clinically meaningful in either direction. For example, a patient with an improvement from #4 (oxygen supplementation, hospitalized) to #2 (discharged, no oxygen) is clearly relevant. Also, a change from #5 (high flow oxygen) to #3 (hospitalized but no supplemental oxygen) is clearly relevant as well. Of note, inclusion criteria of the trial determine that all patients to be included are either in #4 or #5 at time of inclusion into the trial.

Physicians or nurses record the scale value daily at the same time. The time can be fixed individually for each patient. Recordings are obtained +/- one hour of the intended time.

### **7.3.2 Oxygen saturation (SaO2) while breathing ambient air**

Oxygen saturation while breathing ambient air will only be analysed for patients with an ordinal scale value below 5. Patients requiring supplemental oxygen are going to be analyzed for SaO2 while breathing ambient air. If SaO2 levels at ambient air drop below 90%, supplementary oxygen is immediately provided again and the amount of oxygen (liter/min) will be recorded that is required to keep SaO2 above 94%. Patients at ordinal scales at 5 or higher will not be analysed this way.

### **7.3.3 Laboratory parameters**

Nose/throat swabs are collected at day 0 and day 1 (before first CP administration) and subsequently at day 2, 3, 5, 7, 10, 14, 28 or until discharge. Serum for SARS-Cov-2 diagnostic is collected at baseline and subsequently at day 3, 7, 14 and once during the follow-up period (between day 35 and day 84). Serum collection on the following days is optional: day 1, 2, 3, 10 and 28. Details on sample collection and schedule will be provided in the laboratory manual.

Nasopharyngeal swabs are analysed for SARS-CoV-2 RNA viral load by semi-quantitative real-time RT-PCR in the laboratory of Prof. [name] (Center for Infectious diseases, University Hospital Heidelberg). Patient serum obtained at the different time points is stored

at -20° C until further use. Antibodies directed against SARS-CoV-2 are going to be analysed in recipient serum before (day1) and after (day 3) treatment. IgG Antibodies are detected in standard ELISA tests. Further, analyses for neutralizing antibodies are performed by [name]. [name] (DKFZ, Heidelberg). Cytokine analyses is performed in the laboratory of PD [name] (NCT Heidelberg) with the Bio-Plex Pro Human Cytokine 48-Plex Screening Panel (Biorad, Munich, Germany). To evaluate the effects of CP onto inflammation and cytokine levels, a first analysis is performed after the first randomized 40 patients. All other serum specimens are analyzed at the end of trial.

